## Abstract

**Background:**

Accidental falls in hospitals are serious events concerning the safety of the patients. Recent studies demonstrated that the time of falls is a key factor to be considered in prevention. It has been shown that the time of day, the day of the week and the month of the year impact on the occurrence of falls. The aim of the study is to determine the effect of the application of a programme of preventive measures based on the temporal patterns of the risk factors on the hospital fall occurrence.

**Methods:**

A mixed-method research design. The following three phases will be carried out: 1) Longitudinal prospective study in two parts: (a) audits and seminars of healthcare professionals focused on an effective and efficient hospital falls register. Multi-Component and Single Cosinor analyses will be performed to obtain the temporal patterns of hospital falls and their related variables and (b) implementation of a based-temporal patterns, multidimensional prevention programme. 2) Retrospective study of falls registered in institutional databases. 3) Qualitative study based on focus groups (physicians, nurses and nursing assistants). The study protocol was approved in 2018.

**Discussion:**

With regard to the safety of patients, hospital falls are serious events. Recent studies have demonstrated that the time of falls is a key factor to be considered in prevention. It has been shown that the time of day, the day of the week and the month of the year impact on the occurrence of falls. It is imperative to study temporal patterns of hospital falls to effectively and comprehensively define the aetiology of falls and, therefore, design preventive strategies. A reduction of the number of in-hospital falls and related injuries is expected, as well as an improvement in the quality of life of patients. Considering temporal patterns and levels of mood and sleep of healthcare professionals will achieve an improvement in patient safety.

**Trial registration:**

Retrospectively registered in ClinicalTrials.gov ID: NCT04367298.

**Supplementary Information:**

The online version contains supplementary material available at 10.1186/s12912-021-00618-y.

## Background

The proportion of older people in the general population has increased during the last few years. Consequently, an important challenge of the public health system is to preserve the autonomy and independence of this group. One of the greatest causes of loss of autonomy and independence are accidental falls and related injuries. Epidemiology shows that accidental falls are not only a main and common problem among older people all around the world but also a big issue in terms of social and economic repercussions for the victims and their families. [1]

Hospital falls imply a greater challenge for healthcare organizations due to their effect on the patient’s quality of life (due partly to the loss of autonomy and independence). In addition, they increase morbidity and length of stay in hospitals, leading to an important rise of the sanitary outlay [2, 3].

Falls in older people are due to intrinsic and extrinsic factors [4]. Even though many studies have been conducted to identify the causality of falls, the time of falls is often not considered [5]. Evidence suggests temporal patterns in the occurrence of hospital falls [6]. Research in temporal patterns in the manifestation and intensity of symptoms and risk of life-threatening and life-ending events (chronopathology and chronorisk) is essential to develop longitudinal (chrono)preventive and (chrono)therapeutic interventions and strategies that take into account the aforementioned patterns [7, 8]. Therefore, this study aims to implement longitudinal preventive counter-measures based on temporal patterns of incident events and relative risk factors for falls and related injuries (*chronoprevention*).

The risk of fall is directly correlated to ageing, so the number of accidental falls will proportionally grow with the ageing of general population [4, 9]. Recent studies show that 30 % of people living among their communities suffer one fall per year [10], rising to 40 % among hospitalized people [11]. Regarding hospitalized people, fall rates show a great variability, between 2 and 17 falls per 1,000 occupied beds [12, 13].

Accidental falls are the result of a complex interaction of multiple risk factors [4]. Lately, numerous epidemiological studies about accidental falls have identified intrinsic risk factors (biological and behavioural), such as age, chronic medical conditions, drug adverse effects and wrong lifestyles, and external risk factors (socioeconomic and environmental, a large part of which are modifiable), for instance, housing quality and design, house surface and illumination [14–16]. According to Cameron [17], an effective intervention, even when only assessing one associated risk factor, could reduce both the number of events and the associated morbidity [18].

### Temporal patterns in hospital falls and relative risks of fall

Although important efforts have been made to identify possible risk factors for falls, the time of falls has often been ignored. With regard to the occurrence of accidental falls, it is important to know not only the time of day and the shift work of the healthcare professionals (especially nurses, who are responsible for the data collection) but also the relative risk of intrinsic and external factors (*chronoepidemiology*), as well as circadian rhythms related to the clinical care of patients and healthcare workers [19, 20]. Recent studies of our research group [5, 20, 21] observed that the time of the day, the day of the week and the month of the year have impacts on the fall occurrence. Concretely, a retrospective study [20], carried out in five different non-teaching public Italian hospitals after the development of a programme to prevent falls, identified 24-hour and seasonal patterns for accidental falls in hospitals among a population older than 65 years old and showed crucial information about the relationships between the circumstances of falls (cause, mode and place) and times of falls. On the other hand, the extension of preventive measures according to the obtained temporal patterns (*chronoprevention*) affected the reduction of the number of falls in hospitals, although, due to the retrospective nature of the study and the association with other institutional measures not included in the study, a possible direct effect was not established.

In addition to the research carried out in our group, several studies have been focused on the topic, which is an important indicator of the increasing importance of the research field among the scientific community [22, 23]. Both studies confirmed the finding of a morning peak in hospital falls strictly related to bathing activities. In fact, as consequence of the results published by Magota [23], a letter to the editor was published in order to promote more comprehensive research about accidental falls focused on temporal patterns [24].

It is important to emphasize that some patient characteristics, such as number and type of medical conditions, have some influence on the time of falls in hospitals [7, 20]. The type of drug has some influence on the temporal pattern of falls [8]. Nevertheless, it is important to understand whether the administration time of the drug has an influence on the fall occurrence and, therefore, to reduce its incidence. This is why understanding the temporal differences in the administration of hypertension drugs led to a reduction of different clinical conditions (cardiovascular diseases, diabetes mellitus or kidney failure) [25].

### In-hospital falls and registration culture

Documenting and collecting data about the causes and circumstances of accidental falls is fundamental to produce an optimal preventive programme. Another study [26] proved not only the lack of data collecting about accidental falls in Spanish hospitals and community settings but also the lack of registration of the fall. This is probably because most of the falls do not require medical attention or they have not been witnessed. Moreover, healthcare personnel perceive that registration of the fall is a nurse’s task, or they totally ignore that something should be done. Another key factor is the excess load of work of the healthcare staff, and therefore, the lack of time to properly produce an appropriate register. Hence, it is important to support, teach and educate healthcare personnel about proper fall documentation, including the circumstances. In this sense, the improvement of an intuitive, simple and uniform system would allow the register to be used successfully, leading to the possibility, a posteriori, of research and data collecting and analysis about temporal patterns, which could create a more appropriate perspective of risks and fall-related injuries in this population [27].

### Chronoprevention: a nursing intervention

To our knowledge, there are no epidemiological studies proposed with a chronobiological approach to demonstrate the influence of preventive counter-measures adjusted to temporal patterns on the incidence of accidental falls [28]. Therefore, it is necessary to develop prospective studies in order to confirm temporal patterns in hospital falls and to fully understand intrinsic and extrinsic risk factors.

Lastly, the temporal patterns of the professional team, including the number of qualified workers, the fulfilment of patient caring tasks and the characteristics of their work schedule, form another important factor to be considered during the examination of time patterns in accidental falls in hospitals.

Generally, healthcare worker teams are reduced in number during night shifts, weekends and holidays [21]. Some programmed tasks and activities of patient care have an influence on the progress of the fall, such as bed sheets changing, bathing, feeding or transferring [20].

Besides, the roles of fatigue/sleepiness, attention and cognitive functionality in healthcare professionals, just like disruptor agents of circadian time structure (i.e. shift work, night shift, etc.), could affect the vigilance and attention to falls during the day and night. Therefore, it is necessary to evaluate the aforementioned variables in order to define effectively and efficiently the aetiology of falls and, based on emerging temporal patterns, to implement preventive measures in order to reduce the occurrence of hospital falls.

## Methods/design

### Aims

The main aim of this study will measure the effect of the implementation of a falls prevention programme based on temporal patterns and relative risks factors.

Secondary aims will be: (i) to identify temporal patterns in the incidence of hospital falls and intrinsic and external risks factors, pre- and post-intervention; (ii) to establish differences in temporal patterns according to the hospital setting (teaching or non-teaching) and the different types of wards (medical, surgical or mixed), pre- and post-intervention; (iii) to study the role of circadian time in drug administration for older people suffering from hospital falls, pre- and post-intervention; (iv) to identify the level of fatigue/sleepiness, attention and cognitive functionality of healthcare professionals intervening during hospital falls, pre- and post-intervention; and (v) to develop a uniform, simple and intuitive method to record hospital falls in order to improve the effectiveness of the registration of falls and to assess the implementation pre- and post-intervention.

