### Participants and setting

***Phase 1.*** The study subjects will be all those patients over 65 years of age who suffer one/several fall(s) during their admission to the Reina Sofia University Hospital in Córdoba and in the three regional hospitals of the Province of Córdoba (Cabra, Montilla and Pozoblanco) from January 2018 to September 2020.

Specifically, for the study of the levels of fatigue/sleepiness, attention and cognitive functionality of the healthcare professionals, the reference nurses of the older person who has an in-hospital fall during the study period will also be included.

***Phase 2.*** Institutional records of falls occurring in patients over 65 years old. In order to contrast with the prospective design, the institutional records of the four hospitals will be collected during the same period (January 2018 to September 2020).

***Phase 3.*** Healthcare professionals (doctors, nurses and nursing assistants) will be interviewed.

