### Inclusion and exclusion criteria

***Phase 1.*** Regarding patients, they should have been admitted in the aforementioned hospitals, should be over 65 years old and suffer an in-hospital fall. Furthermore, they should sign an informed consent accepting to participate in the study.

Healthcare professionals should have the following requirements: to sign an informed consent accepting to take part in the study and to be nurses in charge of the care of older people suffering from hospital falls, despite not witnessing the event.

Patients who suffer from hospital falls and healthcare professionals who take care of them will be included in the study continuously, which means after every single fall event.

In both cases (patients and healthcare professionals), the sampling will be total.

***Phase 2.*** Records of falls suffered in patients over 65 years old collected in different institutional databases (adverse event report, clinical record of the patient…) in the four hospitals. As in phase 1, the sampling will be total.

***Phase 3.*** Selection of healthcare professionals will be intentional and with the leverage of the collaboration with the centres involved. One person for each sector (doctors, nurses and nursing assistants). Inclusion criteria will be: (i) healthcare professional who has worked in the four hospitals during the time the longitudinal study is carried on; (ii) professionals of clinical units where hospital falls will be recorded during the longitudinal study; and (iii) professionals of clinical units in that are important to the risk of in-hospital falls, by pathologies, dependence, motor or mobility disorder, etc.

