### Data analysis

***Phases 1 and 2.*** For the analysis of quantitative data, descriptive statistics will be used, including measures of frequency, central tendency and dispersion according to the type of variable (quantitative or qualitative). Normality will be calculated with Shapiro-Wilk’s test and homogeneity with Levene’s test. To compare proportions of categorical variables, the chi-square test for contingency tables will be used. In the case of 2 × 2 tables, such tests with Yates correction will be used, and if the expected frequency is ≤ 5, Fisher’s exact test will be used. To compare mean values between the quantitative variables of two groups, Student’s t test for independent samples will be used. For the comparison of the mean values between quantitative variables and hospitals, the one-factor ANOVA test and ad-hoc tests with correction by GT2 Hochberg (if variance is homogeneous) or Games Howell (if variance is unequal) will be used. For the correlation between the quantitative variables, Pearson’s correlation coefficient will be used. For the logistic regression, multivariate analysis will be used.

All hypothesis tests will be bilateral. All tests with a confidence level of 95 % (p < 0.05) will be considered statistically significant.

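### Secondary aim (ii) sets out to establish teaching versus non-teaching differences from four hospitals, apparently one against three, which the design cannot separate from differences between individual hospitals

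*Protocol article*

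**What the plan says.** The Aims section of the protocol article gives secondary aim (ii) as "to establish differences in temporal patterns according to the hospital setting (teaching or non-teaching) and the different types of wards", both before and after the intervention.

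Participants and setting lists the sites for Phase 1 as "the Reina Sofia University Hospital in Córdoba and in the three regional hospitals of the Province of Córdoba". Phase 2 uses the same sites: "the institutional records of the four hospitals will be collected during the same period". Nowhere does the article state whether any regional hospital is a teaching hospital.

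Patients and nurses "will be included in the study continuously, which means after every single fall event", and "In both cases (patients and healthcare professionals), the sampling will be total". No number of falls is planned or forecast.

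Data analysis gives a general list of two-sided tests at 0.05: chi-square (with Yates or Fisher variants), the independent-samples t test, Pearson correlation and logistic regression. It adds an analysis by hospital: "For the comparison of the mean values between quantitative variables and hospitals, the one-factor ANOVA test". Temporal patterns are to be explored by Cosinor analysis, whose F test addresses zero amplitude within one series. No test is assigned to the teaching versus non-teaching contrast.

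The Limitations section says that the intervention is adapted to the cases of each centre. It does not mention that only one site appears to be a teaching hospital.

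**The concern.** To establish a difference by setting is to say something about teaching status as such. That needs several hospitals of each kind, so that what the teaching hospitals share can be told apart from what is peculiar to one of them. Here one side of the comparison appears to be a single hospital.

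The article itself gives reasons to expect hospitals to differ in the timing of falls for other causes. In the Background it ties falls to staffing by shift and to timed care tasks such as bathing and feeding, and it reports that fall registration is incomplete. After the intervention, each centre also has its own tailored programme. A difference in the daily pattern between the university hospital and the other three could come from any of these.

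At stake is a published statement that teaching hospitals have a different temporal pattern of falls, when the data show only that one hospital differs from three others.

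**Working it through.** There is no figure in the article to reproduce: it states no sample size, power, fall count or intraclass correlation (ICC). The checks below use the four hospitals and the two-sided 0.05 level from the article. Everything else is marked as an assumption.

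**1. Can teaching status be separated from hospital?** Code teaching = 1 for the university hospital and 0 for the three regional ones (inferred split).
- Intercept, teaching indicator and university-hospital indicator: 3 columns, rank 2. The last two columns are identical.
- Intercept, teaching indicator and three hospital indicators: 5 columns, rank 4. Four hospitals give only four distinct rows, so the rank cannot exceed 4 under any split.

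More falls add repeated rows, not rank.

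**2. What could a hospital-level test show?** Permute the teaching label over the four hospitals.
- One against three: C(4,1) = 4 assignments, so the smallest p is 1/4 = 0.25.
- Two against two: C(4,2) = 6 assignments. Swapping the groups gives the same absolute difference, so the smallest two-sided p is 2/6 = 0.33.

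Neither can reach 0.05.

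A hospital-level t test has 4 − 2 = 2 degrees of freedom and a critical value of 4.30 instead of 1.96. For one against three, the standard error is SD × √(1 + 1/3). Solving the noncentral t for 80% power gives a detectable difference of about 6.5 SDs of the hospital-level values. Such a test can reach 0.05 in principle, but only under a normal model and for a very large gap. Even then, under one against three, it would show only that this hospital is unusual.

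**3. What if individual falls were tested instead? (Conditional.)** With m falls in each of the four hospitals, clustering multiplies the variance of the contrast by DE = 1 + (m − 1) × ICC. The true type I error of a nominal 0.05 test is then 2 × [1 − Φ(1.96/√DE)]. Taking m = 100 and the ICC as assumptions:

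| ICC | DE | True type I error |
|---|---|---|
| 0 | 1.00 | 5.0% |
| 0.005 | 1.50 | 10.9% |
| 0.01 | 1.99 | 16.5% |
| 0.02 | 2.98 | 25.6% |
| 0.05 | 5.95 | 42.2% |

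Over ICCs of 0.005 to 0.05 the range is 7.9% to 29.1% with 50 falls per hospital, and 25.7% to 66.8% with 400. A simulated Yates chi-square test (20,000 runs, 100 falls per hospital) gave 8.8% to 40.5% over the same ICCs, and no inflation (3.6%) with an ICC near 0. These figures show what could happen. They do not describe a test that the article commits to.

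**The case against.** **The article assigns no test to this contrast.** A reader might infer that falls will be pooled by setting and tested as independent, with an inflated false-positive rate, because the general list includes the chi-square test and says that the "t test for independent samples will be used". The documents do not support that reading. The method given for temporal patterns is Cosinor analysis, and the ANOVA compares hospitals as hospitals, which is close to the presentation recommended here. The type I error figures above also rest on assumed fall counts and ICCs. This objection stands: those figures remain conditional.

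**The comparison may be meant locally.** The article expects its findings to be useful to the institution. For these four named hospitals, a stable difference between them is real and not a false positive. That is fair, and it removes the type I argument under that reading. But a local comparison is a statement about hospitals, and aim (ii) is worded as one about setting.

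**The one against three split is inferred.** Correct. With two against two, teaching status would no longer coincide with a single hospital. There would still be only 2 degrees of freedom, and the permutation floor would rise to 0.33.

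**Ward type.** A reader might infer that ward-type contrasts are confounded by hospital in the same way. The article gives neither the ward mix of any hospital nor the terms of its models, and a condensed article may leave model terms to the full protocol. No error on ward type is shown.

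**A later analysis plan could deal with it.** It could choose a test, but it could not add hospitals. The aim and the site list together fix what can be concluded.

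**Conclusion.** The point holds in a limited form. Aim (ii) promises a conclusion about teaching status that four hospitals cannot support. If, as the names suggest, only the university hospital is a teaching site, the confounding is complete and depends on no assumed number. With hospital as the unit, the permutation p-value cannot fall below 0.25 (one against three) or 0.33 (two against two).

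It is not shown that the trial will report a falsely significant teaching effect: that would need fall-level tests of this contrast and between-hospital variation above zero, and the article states neither. This is a minor point on one part of one secondary aim. The main pre/post comparison is untouched.

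**What to change.** - Reword aim (ii) so that it describes temporal patterns in each of the four named hospitals, before and after the intervention.
- State which of the four are teaching hospitals.
- Draw no test-based conclusion about teaching status. Adding a random hospital effect would not rescue the inference with four hospitals.
- List the apparent single teaching site as a limitation, and note that the post-intervention contrast also carries each centre's tailored programme.
- Optionally, present ward-type contrasts within hospital. This is sensible practice and not the correction of a demonstrated error.

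The cost is a change of wording in one secondary aim and in the limitations, and the loss of the claim about teaching status. No data collection changes.

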### Study variables

The main dependent variable will be the number of hospital falls. A hospital fall will be defined as “the consequence of a non-intentional and sudden movement towards the floor from a more elevated position” in hospital settings.

Other independent variables related with the patient who experiences a hospital fall include: (i) sociodemographic and economic data (age, gender, marital status and level of education); (ii) time (hour and minute, day and shift work) of fall; (iii) patient position (from the bed with or without bedrails, sitting, walking, and so on) and witness of the fall (roommate, family member, healthcare professional or no witness); (iv) use/no use of footwear and kind (open or closed); (v) cause of fall (instability (general instability and balance loss), dizziness (syncope, fainting and cardiovascular accident), drug adverse effects (diuretics, anti-hypertension and other drugs), accident (event with no identifiable cause), ambient-related (dropped objects, obstacles and wet floor), fragility (extreme fragility or weakness) or others); (vi) location of the fall (hospital room, bathroom, corridor, public area or others); (vii) fall-related injuries and severity (no wound/no consequences, minor wounds (grazes and minor contusions), afflicting wounds (contusions requiring stitches, fractures and skull trauma) or others (not afflicting wounds but still in need of minor medical intervention)); (viii) number and kind of coexisting clinical conditions; (ix) prescribed drugs and their time of administration; (x) chronotype measured by the Horne-Östberg Questionnaire (1976); (xi) quality of life in terms of body functionality, physical limitations, body pain, social role or function, mental health, emotional limitations, vitality, energy or fatigue and general perception about own health; and (xii) general health status in terms of somatic symptoms, anxiety, insomnia, social dysfunction and depressive symptoms.

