In the case of healthcare professionals, independent variables will be: (i) sociodemographic and economic data (age, gender, marital status, level of education, work experience and time worked in the unit); (ii) kind of contract and work unit; (iii) sleep pattern (quality and quantity of hours); (iv) chronotype measured by the Horne-Östberg Questionnaire (1976); (v) quality of life in terms of body functionality, physical limitations, body pain, social role or function, mental health, emotional limitations, vitality, energy or fatigue and general perception about own health; (vi) general health status in terms of somatic symptoms, anxiety, insomnia, social dysfunction and depression; and (vii) fatigue/sleepiness, attention and cognitive functionality.

Pre- and post-intervention will be:

***Step 1.*** Before implementing preventive measures: development of audits and seminars in order to improve, secure and control the registration of falls in hospitals and related factors, as well as others study variables (quality of life, functional status, chronotype, fatigue/sleepiness, attention and cognitive functionality). These interventions will be carried out by research nurses who are working in hospitals.

***Step 2.*** Implementation of a preventive measures programme: adjusted to the identification of temporal patterns of falls and relative risk factors of falls. As measures will be agreed with the managers of hospital centres, the interventions will be reflected in the official document of general objectives of the hospitals. Official document to which the personnel involved in the intervention have access. Preventive measures will be focused on organizational, educational and behavioural elements related to older people and healthcare professionals:

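### Aim (iv): the crude pre/post comparison of nurse fatigue at falls can move with the shift mix of falls alone, so a within-shift comparison should be reported beside it

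*Protocol article*

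**What the plan says.** The contrast is set under Aims: "to identify the level of fatigue/sleepiness, attention and cognitive functionality of healthcare professionals intervening during hospital falls, pre- and post-intervention".

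Who is measured is set in three places:
- Participants and setting says that "the reference nurses of the older person who has an in-hospital fall during the study period will also be included".
- Inclusion and exclusion criteria says that patients and professionals "will be included in the study continuously, which means after every single fall event".
- Data collection: Procedure adds that these measures will be known only for the professionals responsible for the patient who fell. No nurses are sampled outside falls.

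Study variables (Step 2) describes the programme as "adjusted to the identification of temporal patterns of falls and relative risk factors of falls". One of its listed measures concentrates effort around meals and transfers. Another monitors and improves how work shifts are distributed among staff.

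The same section records, for each fall, "time (hour and minute, day and shift work) of fall". Data collection: Instruments names the Epworth Sleepiness Scale for somnolence, fatigue and speed of response.

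Data analysis states: "To compare mean values between the quantitative variables of two groups, Student’s t test for independent samples will be used". The only multivariable method named is a logistic regression, with no outcome or covariates given. Tests are two-sided at 0.05.

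**The concern.** Because a fall triggers each nurse measurement, the shift mix of the measured nurses is the shift mix of the falls. A programme adjusted to the times of falls may prevent more of them at some hours than at others. The falls that remain would then come from a different mix of shifts. If nurses at night falls score differently from nurses at day falls, the overall mean moves with the mix.

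At stake is the interpretation of aim (iv). A reader who sees a pre/post difference in nurse sleepiness would naturally take it as a change in the staff, when it may reflect only when the remaining falls happened.

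**Working it through.** The article gives no nurse score mean or SD, no shift distribution and no expected number of falls, so there is no figure of its own to reproduce. What follows is an identity and two illustrations. Every numerical input is an assumption unless marked otherwise.

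**Identity.** Pooled mean = Σ pₛ μₛ, where pₛ is the share of falls in shift s and μₛ the mean score of nurses at falls in that shift. If no μₛ changes, post minus pre = Σ (pₛ,post − pₛ,pre) μₛ. This is zero when all μₛ are equal or when the shares do not change.

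**A worked case.** Assume 30% night falls before, mean scores of 11 (night) and 8 (day), day falls cut by 40% and night falls not cut.
- Night share after = 0.30 / (0.30 + 0.70 × 0.60) = 0.30 / 0.72 = 0.417.
- Crude mean before = 0.30 × 11 + 0.70 × 8 = 8.90.
- Crude mean after = 0.417 × 11 + 0.583 × 8 = 9.25, a rise of 0.35 with no change in either shift.
- Standardised to the 30/70 mix, both periods give 8.90, a difference of 0.
- If falls instead drop by 20% in both shifts, the night share stays at 0.30 and the artefact vanishes.

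**Illustration 1.** Assume a night share before (n) of 30% or 40%; non-night falls cut by 30% or 50% and night falls by 0%; a night/day gap of 2 or 4 points; an overall SD of 4; and 300 falls before. The step lengths of 18 and 15 months come from the Design section.
- Night share after = n / (n + (1 − n)(1 − cut)): 0.38 (30%, cut 30%), 0.46 (30%, cut 50%), 0.49 (40%, cut 30%), 0.57 (40%, cut 50%).
- Movement of the mean = change in share × gap. Smallest: 0.080 × 2 = 0.16 points. Largest: 0.171 × 4 = 0.69 points.
- Falls after = 300 × 15/18 × remaining fraction. For the smallest case, 250 × 0.79 ≈ 198. For the largest, 250 × 0.70 = 175.
- Standard error = 4 × √(1/n₁ + 1/n₂). Smallest case: 4 × √(1/300 + 1/198) = 0.37. Largest: 4 × √(1/300 + 1/175) = 0.38.
- Two-sided rejection rate by normal approximation: 7% in the smallest case and 44% in the largest.

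**Illustration 2.** Assume a within-shift SD of 1, a gap g in SD units, and n falls in each period. Movement = g × change in night share. SE = √[(v₀ + v₁)/n] with v = 1 + g²p(1 − p).

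| Night share | Gap (SD) | Movement (SD) | Rejection, n = 200 | Rejection, n = 400 |
|---|---|---|---|---|
| 30% to 50% | 0 | 0 | 5.0% | 5.0% |
| 30% to 50% | 0.2 | 0.04 | 6.8% | 8.7% |
| 30% to 50% | 0.5 | 0.10 | 16.3% | 28.0% |
| 30% to 50% | 0.8 | 0.16 | 32.1% | 56.1% |
| 40% to 25% | 0.5 | −0.075 | 11.3% | 17.8% |

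The last row shows that the direction depends on which hours improve.

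**Cost in precision.** With equal numbers per period and a night share going from 30% to 50%, the correlation between period and night is r = 0.10 / √(0.40 × 0.60) = 0.204. The variance of the period effect is inflated by 1 / (1 − 0.042) = 1.043, about 2% on the standard error, before any gain from removing between-shift variance.

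**The case against.** The case on the other side is substantial.

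- **Aim (iv) is descriptive.** It asks for the level among nurses at falls, and the background says these variables serve to explain why falls occur. For that purpose the level with whatever shift mix falls have is the right quantity. This stands, and it is why the crude result should be kept. The problem begins when the two levels are compared and read as a change in staff.
- **The list of tests is generic, and a statistical analysis plan not shown may add shift.** This also stands. The point is not that a covariate list is missing. Sampling triggered by falls, a time-adjusted programme and an unadjusted two-group test do not by themselves separate a change in mix from a change in nurses.
- **A reader might infer that the programme is designed to change when falls happen.** The article does not say so. Its goal is fewer falls, and most of the listed measures, such as footwear, reminders and safe mobility, are not tied to a time of day. Falls may drop evenly across shifts.
- **A reader might infer that the article expects nurses at night falls to be more fatigued.** It only lists fatigue among possible influences on vigilance, "just like disruptor agents of circadian time structure (i.e. shift work, night shift, etc", and gives no difference between shifts. If the same nurses rotate through all shifts, the gap may be small.
- **Adjusting for shift is not neutral.** The programme also acts on the distribution of work shifts, so conditioning on the shift of the fall could remove part of its effect. Selection through falls also remains within each shift. This stands and shapes the fix.

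**Conclusion.** The concern holds in conditional form. Two conditions are needed together: the shift mix of falls must change, and nurse scores must differ by shift. The article makes both plausible but quantifies neither. If both hold, the unadjusted comparison can show a difference with no change among the nurses of any shift.

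The range of 0.16 to 0.69 points and 7% to 44% rejection rests wholly on assumed inputs. Its top end needs a night/day gap of one full SD and no reduction at all in night falls. It would go too far to say that nurses will look more fatigued after the programme, or that a true effect would be reversed. The direction depends on which hours improve, and no true effect has been posited against which a reversal could be shown.

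This is a proportionate improvement to a secondary analysis. It does not affect the main outcome, the number of falls.

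**What to change.** For aim (iv):

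1. Keep the crude pre and post levels, labelled as a description of nurses at falls.
2. Add a within-shift comparison: a linear model for the score with period and the recorded shift of the fall, or period means standardised to one fixed shift mix.
3. Report the shift mix of falls in each step beside both results.
4. State that the two results answer different questions, because the programme also acts on the distribution of work shifts. Base any statement about a change in nurse fatigue on the within-shift result, and note that selection through falls remains.

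The authors should also state plainly that the nurse measures are collected after the intervention. Data collection: Procedure describes obtaining them during the first 18 months, while aim (iv) needs both periods.

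The shift of each fall is already recorded, so no new variable is needed. The cost is one extra term in a secondary analysis and a slight loss of precision.
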